### 2.4. Eligibility Criteria

#### 2.4.1. Inclusion Criteria

The study will include adults aged between 19 and 65 years who have undergone gastrointestinal endoscopy, have not been diagnosed with other gastrointestinal diseases, and have been diagnosed with FD according to the Rome IV criteria. Participants must have experienced persistent symptoms for a minimum duration of three months, with the onset of these symptoms occurring at least six months prior to the study. Additionally, all participants will need to provide written informed consent before their inclusion in the study.

#### 2.4.2. Exclusion Criteria

The exclusion criteria for the study are as follows: participants with gastrointestinal structural diseases diagnosed via endoscopy within the past three years and individuals exhibiting alarm symptoms, such as significant weight loss, hematochezia, or dysphagia. The study will also exclude individuals with major psychiatric disorders or neuropsychiatric conditions and serious organic diseases that could affect bio-signals, including heart failure, angina, myocardial infarction, arrhythmia, or valvular heart disease. The use of medications that could influence bio-signals on the day of measurement, such as anticoagulants, vasodilators, and antihypertensives, will be another exclusion criterion. Physical conditions that would impede the attachment of biometric sensors, such as skin disorders at the sites where electrodes will be attached (e.g., wrist), will also result in exclusion. Participants who have undergone gastrointestinal surgery within the past six months and pregnant women will not be included. Additionally, individuals affiliated with the research team, either as students or staff, will not be eligible to participate. Finally, any potential participant deemed unsuitable by the principal investigator due to physical or mental incompatibilities will be excluded from the study during the phone screening and screening visit.

### 2.5. Participant Recruitment

Participants will be recruited through online postings and offline posters at Kyung Hee University Hospital in Gangdong. Flyers will also be sent to patients with FD who participated in previous studies by the same research team and who have consented to be contacted for participation in other studies. Recruitment materials will include detailed information about the study’s purpose, procedures, duration, compensation, and safety considerations.

### 2.6. Study Procedures

The study is organized into two in-person visits. The initial phone screening will be conducted to gather information on recent upper endoscopy and blood test results, symptoms and diagnosis of functional dyspepsia, medical history, medication use, alarm symptoms, and the inclusion and exclusion criteria. Participants deemed eligible for study participation during the phone screening will be invited to attend the first visit, which is dedicated to screening the participants, while the second visit will focus on bio-signal measurements.

During the first visit, participants will be provided with a detailed explanation of the study, and written informed consent will be obtained. Demographic data, medical and surgical history, and current medication use will be collected. Vital signs, including blood pressure, heart rate, and body temperature, will be measured, alongside anthropometric data, such as height and weight. Blood tests and an electrocardiogram (ECG) will be conducted unless results from the past year are available. FD symptoms will be assessed using the Visual Analog Scale (VAS), and a diagnosis will be confirmed through the Rome IV criteria. Eligibility will be determined based on the aforementioned inclusion and exclusion criteria.

The second visit will involve a review of medication use and menstrual cycle details for female participants. The vital signs will be measured again, and participants will complete a series of questionnaires, including the Standard Tool for Pattern Identification of FD [2], Cold–Heat Pattern Questionnaire [26], Deficiency–Excess Pattern Questionnaire [27,28], Phlegm Pattern Questionnaire [29], Food Retention Questionnaire [30], Spleen Qi Deficiency Questionnaire [31,32], Stomach Qi Deficiency Questionnaire [33], Nepean Dyspepsia Index (NDI) [34], State-Trait Anxiety Inventory (STAI) [35], Beck Depression Inventory-II (BDI-II) [36], and the EeroQol-5-Dimension (EQ-5D) [37]. Participants may opt out of answering any questions they find uncomfortable. The Standard Tool for Pattern Identification of FD questionnaire comprises 45 items that categorize FD symptoms into six types: liver–stomach disharmony, dampness and heat in the spleen and stomach, spleen and stomach deficiency and cold, tangled cold and heat, food retention disorder, and insufficiency of stomach yin. This questionnaire demonstrates high reliability, indicated by its internal consistency, and a moderate level of validity, based on correlation analyses between the FD patterns identified by the tool, the Rome IV subtypes, and other dyspepsia-related questionnaires [2]. In addition, the Cold–Heat Pattern Questionnaire [26], Deficiency–Excess Pattern Questionnaire [27,28], Phlegm Pattern Questionnaire [29], Food Retention Questionnaire [30], Spleen Qi Deficiency Questionnaire [31,32], and Stomach Qi Deficiency Questionnaire [33] have been developed as pattern identification tools. These patterns are recognized as being significantly related to FD and the tools have been validated for both reliability and validity.

### 2.7. Data Collection

Pattern identification will be conducted by licensed Korean medicine doctors via questioning, tongue diagnosis, pulse diagnosis, and abdominal diagnosis. This assessment determines deficiency–excess, cold–heat, and the presence of phlegm or food stagnation, as well as six primary FD differentiation patterns (spleen and stomach deficiency–cold, spleen Qi deficiency, liver–stomach disharmony, food stagnation, spleen deficiency with damp–heat, mixed cold and heat).

Bio-signal measurements will be conducted during the second visit or during the first visit only if the screening procedures confirm that the participants meet the inclusion criteria. Prefrontal cortex activity will be measured using a headband-type fNIRS device (NIRSIT; OBELAB Inc., Seoul, Republic of Korea). SCR, ECG, and pulse wave signals will be recorded with electrodes attached to the fingers, wrist, and chest, connected to the Biopac MP160 system (BIOPAC Systems Inc., Goleta, CA, USA). Radial artery pulse waves will also be measured using the DMP-LIFE PLUS pulse analyzer (DAEYOMEDI Co., Ltd., Ansan, Republic of Korea). These measurements will be conducted with the participants in supine position for two minutes. To maintain objectivity, the researcher measuring biometric signals will be different from the doctors diagnosing the patients with FD. Additionally, the diagnosis and pattern identification results will be blinded to both the researcher and the participants. Throughout the measurements, participants will be monitored thoroughly for any discomfort or adverse events.

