## Abstract

**Background:** Functional dyspepsia (FD) is a common functional gastrointestinal disorder characterized by chronic digestive symptoms without identifiable structural abnormalities. FD affects approximately 8–46% of the population, leading to significant socioeconomic burdens due to reduced quality of life and productivity. Traditional medicine utilizes differential diagnosis through comprehensive examinations, which include observing and questioning, abdominal examination, and pulse diagnosis for functional gastrointestinal disorders. However, challenges persist in the standardization and objectivity of diagnostic protocols. **Methods:** This study aims to develop an artificial intelligence-based algorithm to predict identified patterns in patients with functional dyspepsia by integrating brain–body bio-signals, including brain activity measured by functional near-infrared spectroscopy, pulse wave, skin conductance response, and electrocardiography. We will conduct an observational cross-sectional study comprising 100 patients diagnosed according to the Rome IV criteria, collecting bio-signal data alongside differential diagnoses performed by licensed Korean medicine doctors. The study protocol was reviewed and approved by the Institutional Review Board of Kyung Hee University Hospital at Gangdong on 25 January 2024 (IRB no. KHNMCOH 2023-12-003-003) and was registered in the Korean Clinical Trial Registry (KCT0009275). **Results:** By creating AI algorithms based on bio-signals and integrating them into clinical practice, the objectivity and reliability of traditional diagnostics are expected to be enhanced. **Conclusions:** The integration of bio-signal analysis into the diagnostic process for patients with FD will improve clinical practices and support the broader acceptance of traditional-medicine diagnostic processes in healthcare.

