## 1. Introduction

Diagnosis and prognosis are critical parts of the medical process, with treatment and follow-up management strategies based on the diagnosis of a disease. In traditional medicine, such as traditional Chinese and Korean medicine, instead of identifying the disease itself, a pattern of symptoms is identified based on overall health conditions, including disease-related symptoms (e.g., gastrointestinal symptoms) and other lifestyle factors (e.g., working hours, sleep patterns, constitution, etc.) and subjective experiences that may not be detected by diagnostic medical devices (e.g., endoscopy, blood tests). This approach is known as the pattern identification method [1]. Based on the identified pattern, Korean medicine doctors prescribe herbal medicine, acupuncture, and manual therapies such as Chuna. Generally, Korean medicine is used primarily for musculoskeletal disorders, functional gastrointestinal disorders, and psychological conditions. In Korean medicine, functional dyspepsia (FD) is diagnosed using a technique involving four phases of examination: interview and observation, listening and smelling, questioning, and palpation. However, key diagnostic methods such as tongue diagnosis, pulse diagnosis, and abdominal diagnosis remain subjective and lack standardization. Recent advancements have included the development of standardized questionnaires to facilitate quantitative assessments for patterns, such as spleen and stomach deficiency–cold pattern, spleen and stomach damp–heat pattern, and food stagnation pattern in patients with FD [2]; However, diagnostic protocols used in clinics still heavily rely on these four examinations. Pulse diagnosis is a cornerstone in traditional medicine for determining conditions such as deficiency–excess (deficient or excessive energy level) and cold–heat patterns. For this examination, doctors continue to rely on their tactile perception, and various medical subdisciplines propose different methods for palpation and interpretation of these subjective sensations, leading to variability and challenges in objective assessments [3,4]. FD poses a significant challenge in healthcare due to its chronic nature and the lack of standardized, objective diagnostic tools. The diagnostic process remains largely reliant on the practitioner’s expertise and interpretation, leading to variability in diagnosis and treatment outcomes. Additionally, there is a critical gap in integrating objective, quantifiable data into the diagnostic process to enhance accuracy and consistency in the diagnosis of FD. Thus, a new approach is needed to address this gap by developing more comprehensive and data-driven diagnostic models.

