### 2.8. Statistical Analysis

Categorical variables include pattern identification results diagnosed by the Korean medicine doctors and those obtained from questionnaires for pattern identification. These variables will be used for subgroup analyses and as outcomes for AI-based prediction models, facilitating comparisons of differentiation patterns based on specific diagnostic results and bio-signals.

The questionnaire results of the NDI, STAI, BDI-II, and EQ-5D will be treated as numerical variables. The normality of the questionnaire results will be assessed to determine suitable statistical tests. Depending on normality, statistical tests like *t*-tests, analysis of variance, or non-parametric tests will be used to compare groups. Subgroup analyses will compare bio-signals between different diagnostic patterns. Correlation analyses will explore the relationships between the questionnaire results and categorical variables, while mediation and moderation analyses will assess potential factors that mediate or moderate the effects among the variables.

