For time-series bio-signals, various machine learning techniques have been shown to be effective in identifying spatiotemporal patterns for predictive and diagnostic tasks [39]. For single-channel signals, such as ECG or SCR, we plan to extract meaningful features that represent the physiological state or detect abnormalities using machine learning models, such as the random forest model. These features include traditional metrics (e.g., R-peak detection and morphological analysis) as well as advanced decomposition techniques (e.g., wavelet transforms and empirical mode decomposition) that facilitate the extraction of time–frequency domain characteristics to capture subtle and non-stationary signal behaviors [40]. Furthermore, deep learning-based methods, including 1D convolutional neural networks (CNNs) and transformer architectures, will be employed for automated and robust representation learning directly from raw signals.

For multi-channel signals, such as fNIRS or pulse wave data, we will utilize both linear and non-linear analytical methods to evaluate signal rhythms and variability. Recently introduced approaches (e.g., network analysis and attention-based models) allow for the modeling of long-term dependencies, revealing spatiotemporal patterns that traditional methods often fail to detect [41,42]. Graph-based models, such as graph neural networks and graph convolutional networks, show potential for analyzing inter-channel connectivity and exploring the functional relationships among multiple bio-signal sources [43]. By leveraging classical connectivity metrics, such as phase-locking values or mutual information, we expect these integrated approaches to yield more accurate and interpretable results.

To address potential confounding variables, we have identified key confounders such as variability in bio-signal measurements, subjectivity in diagnoses, and multi-collinearity among bio-signals. We will use multivariate regression and regularization techniques like Least Absolute Shrinkage and Selection Operator or ridge regression to handle multi-collinearity and apply principal component analysis for dimensionality reduction. Additionally, to ensure our models are based mainly on bio-signals, we will exclude questionnaire scores that strongly correlate with specific patterns. This approach helps maintain model robustness and aligns with our primary study objective.

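### For doctor-assigned patterns, palpated pulse helps make the label and the recorded pulse wave helps predict it; a test against chance cannot show that integrating brain and autonomic signals adds anything

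*Protocol article*

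**What the plan says.** **Label.** Section 2.7: "Pattern identification will be conducted by licensed Korean medicine doctors via questioning, tongue diagnosis, pulse diagnosis, and abdominal diagnosis". The doctors determine deficiency–excess, cold–heat, phlegm or food stagnation, and six FD patterns.

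**Pulse in the label.** The Introduction says of pulse diagnosis: "For this examination, doctors continue to rely on their tactile perception". It also gives the pulse a leading role for two of the predicted outcomes: "Pulse diagnosis is a cornerstone in traditional medicine for determining conditions such as deficiency–excess (deficient or excessive energy level) and cold–heat patterns".

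**Predictor.** Section 2.7: "Radial artery pulse waves will also be measured using the DMP-LIFE PLUS pulse analyzer". The Biopac system records a further pulse channel. The Abstract describes the algorithm as "integrating brain–body bio-signals, including brain activity measured by functional near-infrared spectroscopy, pulse wave, skin conductance response, and electrocardiography".

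**Outcomes.** Section 2.8: "Categorical variables include pattern identification results diagnosed by the Korean medicine doctors and those obtained from questionnaires for pattern identification". Both kinds serve as outcomes of the prediction models.

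**Safeguards.** Section 2.7 keeps the measuring researcher separate from the diagnosing doctors and blinds that researcher and the participants to the pattern result. Section 2.8 adds, for questionnaires: "to ensure our models are based mainly on bio-signals, we will exclude questionnaire scores that strongly correlate with specific patterns".

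**Test.** Section 2.8 compares accuracy and AUC with chance (0.5, 0.33 or 0.17, depending on the outcome) at p < 0.05. It states no comparison between models with and without the pulse.

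**The concern.** The doctor feels the radial pulse and uses it, with three other examinations, to assign the pattern. The model then receives a recording of the same artery. For this outcome, one predictor and one ingredient of the reference label draw on the same physiology, so some agreement is expected whether or not fNIRS, skin conductance or ECG carry information.

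The hypothesis in the Introduction is that signals from brain and body together improve prediction of the differential diagnosis. A test against chance is passed as soon as any one channel is informative. It therefore cannot distinguish integration that adds something from a sensor that agrees with a fingertip. The second is worth knowing, but it is a different conclusion.

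The stated safeguards address other problems. Separate staff and blinding prevent observer influence, not shared physiology. LASSO, ridge and principal components deal with collinearity among predictors, not with overlap between a predictor and the outcome. The exclusion of label-related scores covers questionnaires only.

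**Working it through.** **What the documents supply.** The article gives no figure on this point, so there is none to reproduce. It names four examinations, one of them the pulse. The sample size of 100 equals 2 × 50, the stated minimum per category for a two-category outcome, so I use a 50/50 split.

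**Assumptions (mine).** The doctor's score is the sum of four independent standardised findings, with weight w on the palpated pulse and 1 on each of the others. The label is the sign of that score. The device pulse correlates r with the palpated pulse. All other signals carry no information. This last assumption is deliberate: it asks what the pulse alone can produce.

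**Formulas.** The correlation of the device pulse with the doctor's score is ρ = r·w/√(3 + w²). Then AUC = 0.5 + (2/π)·asin(ρ/√2) and accuracy = 0.5 + asin(ρ)/π.

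Example, w = 1 and r = 0.8: ρ = 0.8/2 = 0.40; AUC = 0.5 + 0.637 × asin(0.283) = 0.68; accuracy = 0.63.

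| r | AUC, equal weight (w = 1) | AUC, pulse double (w = 2) |
|---|---|---|
| 0.1 | 0.52 | 0.53 |
| 0.2 | 0.55 | 0.57 |
| 0.3 | 0.57 | 0.60 |
| 0.4 | 0.59 | 0.64 |
| 0.6 | 0.64 | 0.71 |
| 0.8 | 0.68 | 0.78 |

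**Against the noise at this sample size.** With 50 patients per group, the standard error of an AUC with no signal is √(101/(12 × 2500)) = 0.058. The two-sided 5% limit is about 0.5 + 1.96 × 0.058 = 0.61. At r = 0.1 the pulse effect is lost in noise. At r = 0.6 or more it lies above the limit under either weighting. This is a conventional test of one AUC, used as a yardstick; it is not the t-test in section 2.8.

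**Three models side by side.** A separate simulation of 1,000 trials of 100 patients used one pulse feature, nine pure-noise features and 5-fold cross-validated ridge regression. Here the pulse is given as its share of the variance of the doctor's score; 0.25 is equal weight.

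| Pulse share | r | Full model AUC | Pulse only | Without pulse |
|---|---|---|---|---|
| 0.25 | 0.7 | 0.59 | 0.65 | 0.50 |
| 0.25 | 0.9 | 0.64 | 0.70 | 0.50 |
| 0.40 | 0.7 | 0.64 | 0.69 | 0.50 |
| 0.50 | 0.9 | 0.75 | 0.79 | 0.50 |

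In three of the four settings the full model's average AUC exceeds 0.61, although nothing but the pulse is informative. In the first it falls just short, so passing is possible but not assured. In all four, the full model does no better than pulse-only and the without-pulse model sits at chance. The comparison reveals what a test against 0.5 does not.

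**The case against.** The strongest reply is that the pulse belongs to the hypothesis. The Abstract counts the pulse wave among the brain–body signals, and the Introduction presents device measurement as an answer to subjective palpation. Objectifying the pulse is a stated purpose, and a model that succeeds through the pulse would serve it. That stands. The pulse should stay in, and the pulse-only result is legitimate under its own name. It does not show that combining it with brain and autonomic signals improves prediction.

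Second, a reader might infer that the device reading feeds the label. Nothing in the documents says so. Palpation and recording are separate measurements, made by different people. The overlap is one of shared physiology and is partial.

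Third, section 2.8 also plans questionnaire-derived outcomes, and the tools in section 2.6 are not described as using palpation. So it would be wrong to say that the plan has no label free of the pulse.

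Fourth, the choice of nested models may be left to an analysis plan that is not shown. A missing model list alone would be no finding. The point here concerns the test that section 2.8 does state, which does not match the hypothesis.

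Fifth, the exclusion of questionnaire scores is justified as keeping the models based on bio-signals, not as avoiding circularity. Keeping the pulse wave is consistent with that reason. The rule shows no inconsistency; it simply does not reach this problem.

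Finally, the calculation assumes its weights and correlations. The Introduction stresses how variable palpation is, which makes a low r plausible.

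**Conclusion.** The point holds for doctor-assigned outcomes. Label and predictor share the pulse, and the stated test against chance cannot tell a pulse-driven model from one in which brain and autonomic signals contribute.

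The size is unknown. Over assumed correlations of 0.1 to 0.8, with equal or double weight for the pulse, pulse-only AUC runs from 0.52 to 0.78: from negligible to enough to pass at 100 patients. The range rests on four independent examinations, a 50/50 split and uninformative other signals, none of which the article states.

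Two stronger readings are tempting. One is that any accuracy found will be merely pulse agreeing with pulse; the documents show only that it could be. The other is that fNIRS, skin conductance and ECG have no link to what the doctor feels. That is too strong for ECG: section 2.8 derives heart rate and RR intervals from it, and rate and rhythm can be felt at the wrist.

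**What to change.** In section 2.8, for each doctor-assigned outcome:

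1. Fit three models on the same resampling folds: full, pulse-only, and without pulse (DMP-LIFE PLUS and Biopac pulse channels both removed).
2. Rest any claim that integrating brain and autonomic signals adds predictive accuracy on the gain of the full model over pulse-only, supported by the without-pulse result. Both are needed: with 100 patients, weak extra features can lower the full model's cross-validated AUC, as the simulation shows.
3. Report pulse-only performance as agreement with palpation.
4. Add a sensitivity fit that also leaves out heart-rate and rhythm features from the ECG.
5. Show the questionnaire-labelled outcomes separately.

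This costs a few extra model fits per outcome on data already planned, with no new patients or procedures. The claim for integration may turn out smaller. Fixing the comparison before the data are analysed keeps it from being chosen after the results are seen.

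### Section 2.8 names diagnostic subjectivity as a key confounder, but the measures it lists act only on the predictors and its chance-level test ignores who assigned the label

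*Protocol article*

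**What the plan says.** **Source of the label.** Section 2.7 of the protocol article: "Pattern identification will be conducted by licensed Korean medicine doctors", who question the patient and examine tongue, pulse and abdomen. The Introduction says of these techniques that "key diagnostic methods such as tongue diagnosis, pulse diagnosis, and abdominal diagnosis remain subjective and lack standardization".

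**Use of the label.** Section 2.8 covers both the doctors' pattern results and the questionnaire-derived ones: "These variables will be used for subgroup analyses and as outcomes for AI-based prediction models".

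**Confounders.** Section 2.8 sets out to deal with "key confounders such as variability in bio-signal measurements, subjectivity in diagnoses, and multi-collinearity among bio-signals". It then offers multivariate regression with "regularization techniques like Least Absolute Shrinkage and Selection Operator or ridge regression to handle multi-collinearity", says it will "apply principal component analysis for dimensionality reduction", and leaves out questionnaire scores that track a pattern closely, so that the models rest mainly on the signals.

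**Test.** Section 2.8 compares accuracy and the area under the ROC curve, from bootstrapping and cross-validation, with chance (0.5, 0.33 or 0.17) by a *t*-test at the 5% level.

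**Safeguards.** In section 2.7 the signals are recorded by someone other than the diagnosing doctor, and that person does not see the pattern result.

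**The concern.** The article identifies a specific threat, says it will be handled, and then lists measures that cannot handle it. Shrinkage, principal components and dropping covariates change what goes into the model. They change neither the label nor its dependence on the person who gave it.

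Two kinds of harm are possible, depending on facts the article does not give:

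- **The signals differ by doctor**, for example through session, calendar time or case mix. A model can then gain accuracy by recognising the doctor. A comparison with 0.5 would count that as prediction of the pattern.
- **The signals do not differ by doctor.** Disagreement then acts as label noise and limits how accurate even a perfect model can appear. A modest result is hard to interpret if the reproducibility of the label is unknown.

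The study aims to make pattern diagnosis more objective, so either outcome bears on its main claim.

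**Working it through.** **1. Measures against confounders (section 2.8, with 2.7).**

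| Measure | What it acts on | Acts on the doctors' labels? |
|---|---|---|
| Multivariate regression, LASSO, ridge | Collinear predictors | No |
| Principal components | Number of predictors | No |
| Dropping questionnaire scores | Leakage through predictors | No |
| Separate, blinded person recording signals (2.7) | Signal recording | No |
| Test against 0.5, 0.33 or 0.17 | Model accuracy, all doctors pooled | No |

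**2. The plan's own figures.** The chance levels are 1/2 = 0.50, 1/3 = 0.33 and 1/6 = 0.17, as stated. Section 2.3 asks for at least 50 per category and 100 patients; 2 × 50 = 100, so the total fits a two-class outcome. The illustration below therefore uses two classes and n = 100.

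**3. If the signals vary with the doctor.** All inputs here are assumptions. Two doctors see half the patients each. One calls a pattern in a share *a* of patients, the other in 1 − *a*, so the classes balance overall and 0.5 is the right chance level. The signals carry no pattern information but identify the doctor with accuracy *q*. Then

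expected accuracy = *q*·*a* + (1 − *q*)·(1 − *a*).

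For *a* = 0.6:
- *q* = 0.5: 0.30 + 0.20 = 0.50
- *q* = 0.6: 0.36 + 0.16 = 0.52
- *q* = 0.7: 0.42 + 0.12 = 0.54
- *q* = 1.0: 0.60

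The standard error at chance is √(0.5 × 0.5 / 100) = 0.05. The bound of 0.60 is thus 2 standard errors above 0.5, and 0.52 and 0.54 are 0.4 and 0.8 standard errors above it.

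As a rough stand-in for the planned test, take an exact one-sided binomial test, which rejects at 59 or more correct (actual level 0.044). The probability of apparent success is:

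| Call rates | *q* = 0.5 | *q* = 0.6 | *q* = 0.7 | *q* = 1.0 |
|---|---|---|---|---|
| 0.6 / 0.4 | 0.04 | 0.10 | 0.18 | 0.62 |
| 0.7 / 0.3 | 0.04 | 0.18 | 0.46 | 0.99 |

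A simulation gave the same pattern (n = 100, five features with no pattern information, one of them shifted between doctors, ridge-type classifier, random 5-fold cross-validation, 1000 runs). With call rates of 0.7 and 0.3, mean accuracy was 0.499, 0.510, 0.538 and 0.594 for shifts of 0, 0.5, 1 and 2 SD. With no shift, 8% of runs still reached 0.59, so cross-validated accuracy varies more than the binomial allows and the table is only approximate.

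**4. If the signals do not vary with the doctor.** Take a balanced two-class label and two raters with equal, independent error around an underlying pattern. If each rater is right with probability *p*, agreement is *p*² + (1 − *p*)² = 0.5 + κ/2, which gives *p* = (1 + √κ)/2. For κ = 0.2, 0.4 and 0.6, a perfect predictor of the underlying pattern would match the doctor's label in 72%, 82% and 89% of patients.

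**5. Is holding out a whole doctor a clean remedy?** Not with two doctors. In the same simulation with call rates of 0.7 and 0.3, leave-one-doctor-out accuracy averaged 0.344 with no signal shift and 0.368 with a 2 SD shift. The null value is not 0.5 when call rates differ, so the result cannot be read against chance.

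**The case against.** The strongest reply is that the mechanism depends on facts the article does not give. It speaks of doctors in the plural, but not of how many, how patients are allocated, or whether labels are single or by consensus. A condensed article may leave these details to the full protocol. With one doctor or a consensus label, between-doctor confounding does not arise. Nothing in the article shows that the signals vary with the doctor. The questionnaire-derived patterns are also model outcomes and do not depend on a doctor. All of this stands, and it limits the size of the point.

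A reader might infer two stronger things that the article does not support:

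- **That the plan claims regularisation and principal components cure subjectivity.** It does not say so. It ties the first to collinearity and the second to dimensionality; any link to subjectivity comes only from their place in the paragraph.
- **That the models will learn doctors' habits.** This is possible only under the conditions above, and 0.60 is an upper bound for the assumed call rates.

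The reply does not remove the mismatch. Subjectivity is named as something to be addressed, and no stated measure addresses it. The questionnaire outcomes are not presented as a check on the doctors' labels.

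**Conclusion.** The point holds in limited form. Section 2.8 undertakes to address diagnostic subjectivity, lists measures that act only on predictors, and judges success against a benchmark blind to the doctor. This is a fault in what the article states, and not merely a detail left to another document.

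The size cannot be derived from the article. Under the assumed 40%/60% call rates the apparent accuracy is at most 0.60, and 0.52 to 0.54 if the signals identify the doctor 60 to 70% of the time. If they do not identify the doctor at all, accuracy stays at chance and disagreement only lowers the ceiling. The point calls for a cheap improvement and does not invalidate the study.

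**What to change.** 1. Record a code for the diagnosing doctor with every label.
2. In 2.8, for doctor-assigned labels, replace the fixed-chance *t*-test with a permutation test that shuffles labels within doctor and reruns the whole modelling procedure. This keeps any doctor-label and doctor-signal association in the reference distribution. With one doctor it becomes an ordinary permutation test.
3. Report a doctor-only benchmark beside the model's accuracy and area under the curve.
4. Report the questionnaire-label models alongside, as outcomes that do not depend on the doctor. Give doctor-questionnaire agreement as a descriptive figure only. It is not an accuracy ceiling: the questionnaire is a different instrument, and its errors may be correlated with the doctors', who also question the patient.
5. Give leave-one-doctor-out results only as exploratory, and only if there are several doctors. Stratifying folds by doctor is no substitute, because it leaves every doctor in every fold.
6. Reword the confounder paragraph so that regularisation and principal components are tied to collinearity and dimensionality only, and state separately how subjectivity is handled.

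Cost: one data field, some reruns, and slightly less power from permuting within doctor. The code should be recorded prospectively, since it may not be recoverable later.
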